### Study participants

Patients will be eligible to join the study if they are (1)  $\geq 18$  years of age, (2) living in the community, (3) with a confirmed diagnosis of a prior AMI attack, (4) consent to participate and (5) those who can read Chinese. Individuals who do not understand Cantonese, with impaired communication ability, psychiatric problems or impaired cognitive functioning (i.e. Abbreviated Mental Test  $\leq 6$ ) which may hinder participation in the interventional activities will be excluded. For the RCT study, the sample size is determined on the basis of a large-scale RCT examining the effect of a brief nursing educational intervention on care-seeking knowledge, attitudes and beliefs related to AMI in people with CAD. The effect sizes for knowledge, attitudes and beliefs were 0.39, 0.24 and 0.23 at 3 months after the intervention. In consideration of both clinical relevance and previous study findings, the sample size of this study is determined to give the study adequate power to detect at least a small to medium effect size on the primary outcomes. Using PASS 13 (NCSS, Kaysville, USA), it is estimated that a sample size of 252 subjects per study arm would give the study 80% power at 5%

level of significance to detect an effect size as small as 0.23 on our primary outcomes between the control and intervention arms at the post intervention time points. Further allowing for a potential dropout rate of up to 20%, a total of 315 subjects per arm will be recruited. For the qualitative phase, a criterion sampling of 30 participants who have received the modelling-based narrative intervention will be invited to join on the basis of their prehospital delay time, which will be categorised into three groups:  $\leq 2$  hours,  $> 2$  and  $\leq 6$  hours, and  $> 6$  hours. The criterion is set according to the international AMI management guidelines, where such cut-offs are used to categorise patients into early, intermediate and late responders. A total of 30 participants will be recruited, with 10 participants for each category. Maximum variations in the sociodemographic and clinical profile of the participants will also be adopted in the sampling procedure to illustrate a wider range of data.

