#### **(b) Research plan and methodology**

The aim of the study is two-fold: i) to evaluate the effects of a modelling-based narrative intervention on care-seeking beliefs, attitudes and knowledge, use of ambulance and prehospital care-seeking delays among AIM patients, and ii) to explore how and why the intervention affects the care-seeking behaviours from the patients' perspective. The behavioural intention, as reflected by the care-seeking beliefs and attitudes, are the primary outcomes, while AMI knowledge, use of ambulance and prehospital delays in care-seeking in AMI attacks are the secondary outcomes. The research hypothesis

of the first aim is that AMI patients who receive the modelling-based narrative intervention will report better changes in: i) care-seeking beliefs, ii) care-seeking attitudes, iii) AMI-related knowledge, iv) more likely to use ambulance, and v) shorter prehospital delays when AMI symptoms occur at 3, 12, and 24 months after the intervention, than those who receive didactic education on AMI care-seeking.

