**A didactic education on AMI care-seeking** will serve as the **control intervention**. It consists of one session to be delivered in a small group (6–8 participants/group) format by another RA (RA2). The factual information about AMI and the appropriate response towards possible symptoms will be delivered with a structured PowerPoint slide-set. Narrative approach and booster sessions will not be used in the control group. The intervener will answer questions from the participants when asked, according to the structured education content for the control group. The questions and topics discussed will be recorded for subsequent data interpretation. During the conversation, the RA will not use any wordings which is related to patient's privacy (e.g. patient's name, address etc.) and will only use a subject code to label all the audio records. Permission of audio recording of the conversation will be obtained in the informed consent and before the start of the conversation as well.

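### The 0.23 used for sizing is not supported for a comparison with didactic education, and 252 per arm gives about 73% power at 0.23, not 80%, unless an unstated correlation was used

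*Protocol*

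**What the plan says.** The sample-size text is in the Protocol under Study participants. Its source is "a large-scale RCT examining the effect of a brief nursing educational intervention on care-seeking knowledge, attitudes and beliefs related to AMI in people with CAD", and it reports: "The effect sizes for knowledge, attitudes and beliefs were 0.39, 0.24 and 0.23 at 3 months after the intervention". Beliefs and attitudes are this trial's primary outcomes, and the smaller of their two effects is carried forward. The stated aim is "to detect an effect size as small as 0.23 on our primary outcomes between the control and intervention arms at the post intervention time points", with 252 per arm for 80% power at the 5% level, raised to 315 per arm for up to 20% dropout. The paragraph names two grounds for the choice: "In consideration of both clinical relevance and previous study findings, the sample size of this study is determined to give the study adequate power".

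The contrast is defined elsewhere. The hypothesis in (b) Research plan and methodology is that the narrative arm will do better "than those who receive didactic education on AMI care-seeking". Study interventions describes the control as one small-group session: "The factual information about AMI and the appropriate response towards possible symptoms will be delivered with a structured PowerPoint slide-set". Data analysis makes all tests two-sided at 0.05.

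**The concern.** There are two separate problems in the same paragraph.

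The first is where 0.23 comes from. In the cited trial, education is the treatment under test. In this trial, education on the same subject is what the control arm receives, and each narrative session also opens with a short educational presentation. Whatever both arms gain from being taught cancels out of the comparison. What remains is the increment from modelling, storytelling, extra contact and the booster. The cited trial, as the Protocol describes it, did not measure that increment, and no other section supplies a figure for it.

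The second is arithmetic and does not depend on the comparator: 252 per arm does not give 80% power at 0.23 from the inputs stated.

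At stake is how a non-significant primary result is read. A reader who trusts 80% power at 0.23 will take such a result as stronger evidence against the narrative approach than the design can provide.

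**Working it through.** **Inputs.** Effect 0.23 (standardised), 252 per arm, 80% power, 5% level and 20% dropout come from Study participants. Two-sided testing comes from Data analysis. Equal allocation comes from Study design. Normal quantiles are 1.960 (two-sided 5%) and 0.8416 (80% power).

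**Step 1: dropout.** 252 / (1 − 0.20) = 315. This reproduces.

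**Step 2: size per arm for 80% power.** n = 2 × ((1.960 + 0.8416) / d)².

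- d = 0.23: 2 × (2.8016 / 0.23)² = 296.7, so 297 per arm (298 with the t distribution).
- d = 0.25: 2 × (2.8016 / 0.25)² = 251.2, so 252 per arm.

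The stated 252 matches 0.25, not 0.23. A one-sided test does not explain it: that would need 234 per arm at 0.23, and the Protocol specifies two-sided tests.

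**Step 3: power at 252 per arm.** Power ≈ Φ(d × √(n/2) − 1.960), with √(252/2) = 11.225.

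- d = 0.23: Φ(2.582 − 1.960) = Φ(0.622) = 73%.

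**Step 4: what would rescue 80%.** The variance would have to fall to 252 / 296.7 = 0.849 of its plain value. Three routes give that:

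- baseline adjustment, factor 1 − r²: r = √(1 − 0.849) ≈ 0.39;
- averaging three post-baseline visits, factor (1 + 2r)/3: r ≈ 0.77;
- change from baseline, factor 2(1 − r): r ≈ 0.58.

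The Protocol states none of these correlations.

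**Step 5: sensitivity to the increment over didactic education.** The documents give no figure for this increment, so the values below 0.23 are an assumed range (0.115 is half of 0.23). The middle column uses Step 3. The last column accepts 80% at 0.23, so power ≈ Φ(2.8016 × d/0.23 − 1.960).

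| Net difference | Plain test, 252 per arm | If 80% at 0.23 is accepted |
|---|---|---|
| 0.23 | 73% | 80% |
| 0.20 | 61% | 68% |
| 0.15 | 39% | 45% |
| 0.115 | 25% | 29% |

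The gap between the two columns comes from the unexplained calibration. The fall down each column is what a smaller increment would cost.

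**The case against.** The strongest reply is that power is always conditional on the chosen effect, and that 0.23 can be read as a target difference for this trial's own arms. The paragraph invokes clinical relevance as well as earlier findings, and a target chosen for relevance does not need the source's comparator to match. The narrative arm is also far heavier than a brief education: three weekly sessions of 90 minutes with interactive video and peer modelling, then a half-day booster, against a single slide-based session. The background sections argue, with references, that narrative outperforms conventional teaching.

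Much of this stands. A reader might infer that the comparator makes the expected difference smaller than 0.23, and hence that 80% is overstated for that reason. The documents do not support that step. They do not say what the cited trial's comparator received, so reading 0.23 as education against no education is an inference. Nor do they fix the increment, which could lie below, at or above 0.23. Likewise, the idea that the narrative arm must gain about 0.46 (0.23 + 0.23) over no education holds only if that inference is right and this control session works as well as the cited intervention. Neither is shown.

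What does not stand is the support for the figure. Clinical relevance is named but not argued, the chosen value is exactly the cited beliefs effect, and the case for narrative over teaching is qualitative.

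On the arithmetic, the planned GEE analysis is longitudinal, so a correlation may well have entered the calculation. That would explain 252, but the text does not say so.

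**Conclusion.** The point holds in two parts.

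- The value 0.23 is not justified as the difference between narrative and didactic education. The cited trial, as described, addresses a different contrast, and nothing in the Protocol bridges the two. This is a gap in justification. It is not proof that the true difference is smaller or that the comparator has reduced the power.
- From the stated inputs, 252 per arm gives about 73% power at 0.23, 7 points below the stated 80%; about 297 per arm would be needed. This assumes a plain two-sample comparison with no variance reduction. A baseline correlation near 0.39, for example, would restore 80%.

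If the increment over didactic education were 0.20, power would be 61% (68% on the Protocol's own calibration). At 0.115 it would be 25% (29%). These smaller values are illustrations. That 252 fits 0.25 may tempt a reader to conclude that 0.25 was the value entered, but the documents do not establish this.

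**What to change.** Keep the recruitment target of 315 per arm and revise the sample-size paragraph under Study participants.

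1. Present 0.23 as the target increment over didactic education, with a reason why that size matters, and not as the effect expected from the cited education trial.
2. Do one of the following:
   - restate power at 252 per arm as about 73% at 0.23, 61% at 0.20, 39% at 0.15 and 25% at 0.115, labelled as an assumed range; or
   - state the correlation and method that yield 80% at 0.23, and give the matching values of about 68%, 45% and 29% at the smaller differences.

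The cost is a reworded paragraph and a less favourable stated power. No participants, visits or procedures are added.

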### Study design

This is a sequential mixed-method study consisting of a randomised double-blind controlled trial and an exploratory qualitative study. The study implementation protocol is outlined in Figure 1. A research assistant (RA1) will recruit eligible participants from the cardiac clinics and wards of four regional hospitals in Hong Kong. The study sites are leading hospitals providing cardiac care services within the region. He/she will collect participants' baseline (T0) demographic data and study variables during a face-to-face interview. Block randomisation with a block size of 8, 10 or 12 will be used to ensure even distribution of participants between the two study groups. The block size and the respective allocation sequence to the intervention group receiving a modelling-based narrative intervention (by RA1) and control group receiving a didactic education (by RA2), will be determined by a computer-generated sequence. Participants chronologically recruited to the study will be allocated to the study groups by RA1 according to the computer generated sequence. Another independent RA (RA3), who is blinded to the study group allocation, will collect the post-intervention data. To detect short-term and long-term intervention effects, the outcome variables will be measured repeatedly at 3 (T1), 12 (T2) and 24 (T3) months following baseline data collection for both study groups. This extended period of outcome evaluation permits the study to detect the intervention effects on participants' actual care-seeking behaviours. Previous studies indicated that approximately 16% of these patients experienced AMI symptoms within two years. In the data collection telephone calls, the RA3 will enquire about whether the participants have been admitted to an emergency department with the experience of AMI symptoms. The study participants and their next of kin are strongly advised to contact the RA if they have been admitted due to a possible AMI attack.

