#### Data analysis

For the RCT study, data analysis will be performed on an intention-to-treat basis. Baseline characteristics between the two study arms will be compared by t-test, chi-square or Fisher's exact test

where appropriate. A generalized estimating equation (GEE) model will be used to compare the differential changes on the outcomes across the time points T0, T1, T2 and T3 between the two study arms with adjustment for potential confounding variables. Baseline characteristics with p values < 0.25 for between-group difference will be considered as potential confounding variables. GEE model can account for intra-correlated repeated measures data and accommodate missing data caused by incomplete visits or dropout, provided that the data are missed at random, and thus are particularly suitable for intention-to-treat analysis without the need of imputation for missing data. All statistical analyses will be performed using IBM SPSS 23.0. All statistical tests will be two-sided and a p-value < 0.05 will be considered statistically significant. For the qualitative study, the audio-taped data will be transcribed verbatim. The investigation team will ensure accuracy of the transcription by cross-checking. Content analysis will be adopted to code the qualitative data on participants' perceptions and acceptability of the modelling-based narrative intervention. The analysis will also seek to understand why and how the study intervention influences patients' care-seeking behaviours. The codes units will be organised into categories and subcategories, which will be analysed for emerging themes. The trustworthiness of the qualitative analysis will be enhanced by audio-taping of the interviews, conducting an audit trail, involving two team members to code the qualitative data independently.

**Figure 1.** Study implementation protocol

[figure not shown]

**Figure 2.** Graphical presentation of the modelling-based narrative intervention protocol

[figure not shown]

**Table 1.** The storyline of the narrative video-based virtual heart attack experiencing session

**Background information of the model patient:** **[name]**, 58 year-old man, bus driver, non-smoker, with hypertension and hyperlipidaemia. He sustained a musculoskeletal injury over his chest region a week ago

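### The stated 252 per arm gives about 73% power, not 80%, for an effect size of 0.23 in a two-sided comparison, which would need 298 per arm

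*Protocol*

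**What the plan says.** The Study participants section takes its effect sizes from an earlier large trial of a brief nursing education intervention: "The effect sizes for knowledge, attitudes and beliefs were 0.39, 0.24 and 0.23 at 3 months after the intervention". Beliefs and attitudes are the primary outcomes of this trial; the research plan says that behavioural intention, "as reflected by the care-seeking beliefs and attitudes, are the primary outcomes". So 0.23 and 0.24 are the two effects that matter for power, and 0.39 belongs to a secondary outcome.

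The sample size was computed in PASS 13, and "it is estimated that a sample size of 252 subjects per study arm would give the study 80% power at 5" per cent "level of significance to detect an effect size as small as 0.23 on our primary outcomes between the control and intervention arms", at the time points after the intervention. The enrolment target follows: "Further allowing for a potential dropout rate of up to 20%, a total of 315 subjects per arm will be recruited".

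The sample size sentence does not say whether the test is one- or two-sided, but the Data analysis section does: "All statistical tests will be two-sided and a p-value < 0.05 will be considered statistically significant". Allocation is by blocks and is meant to be equal; the blocks "will be used to ensure even distribution of participants between the two study groups".

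The planned analysis is a GEE model over baseline and the three follow-ups. The sample size paragraph names no PASS procedure, no correlation between repeated measurements, no number of measurements and no covariate adjustment.

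**The concern.** Sample size, power, significance level and effect size are tied together: any three fix the fourth. Here all four are stated, and they do not fit. For a plain two-arm comparison the requirement is about 18% larger than 252 (297/252 = 1.18).

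This matters most if the trial is null. The protocol presents 0.23 as the smallest effect that the trial is powered to find. A reader who sees no significant difference in beliefs or attitudes would take that as the result of a trial with a 20% chance of missing such an effect. On the stated inputs the chance is 27%.

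**Working it through.** **Inputs.** Standardised difference d = 0.23 (SD = 1 on this scale), 80% power and 252 per arm from Study participants; two-sided 5% from Data analysis; 1:1 allocation from Study design. Quantiles: z(0.975) = 1.960 and z(0.80) = 0.842.

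**The plan's figure.** The number per arm is n = 2(z(0.975) + z(0.80))² / d², and 2(1.960 + 0.842)² = 15.70.

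| Effect size and test | Normal approximation | t-test | Reproduces 252? |
|---|---|---|---|
| 0.23, two-sided 5% | 15.70/0.0529 = 296.7, so 297 | 297.7, so 298 | No |
| 0.24, two-sided 5% | 15.70/0.0576 = 272.5, so 273 | 273.5, so 274 | No |
| 0.25, two-sided 5% | 15.70/0.0625 = 251.2, so 252 | 252.1, so 253 | Yes (normal) |
| 0.23, one-sided 5% | 233.7, so 234 | 234.4, so 235 | No |

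Of these, only d = 0.25 gives 252. Solving the other way, the effect detectable with 252 per arm at 80% power is (1.960 + 0.842) × √(2/252) = 0.2496. That 0.25 was the value entered in the software is a possible explanation, but the protocol does not say so and the conclusion does not depend on it. A one-sided test would also contradict the Data analysis section.

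**Power with 252 per arm.** By the normal approximation, power = Φ(d√(252/2) − 1.960).
- d = 0.23: 0.23 × 11.225 = 2.582, and Φ(0.622) = 73.3%; the t-test gives 73.1%.
- d = 0.24: 0.24 × 11.225 = 2.694, and Φ(0.734) = 76.9%; the t-test gives 76.7%.

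Neither primary outcome reaches 80% at its own quoted effect.

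**Dropout.** 252/0.80 = 315, so this step is right and the discrepancy lies in the base figure. Carrying 298 forward gives 298/0.80 = 372.5, or 373 per arm. If all 315 per arm were evaluable, power at 0.23 would be 82%.

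**Could an unstated design feature give 252?** The unadjusted requirement of 296.7 would have to be multiplied by 252/296.7 = 0.849. Equal correlation ρ between all measurements is assumed.
- Baseline-adjusted comparison at one follow-up, factor 1 − ρ²: 252 suffices if ρ is at least √(1 − 0.849) = 0.39.
- Change from baseline at one follow-up, factor 2(1 − ρ): 252 suffices if ρ is at least 1 − 0.849/2 = 0.58. At ρ = 0.5 the factor is 1 and power stays at 73%.
- Mean of the three follow-ups without baseline, factor (1 + 2ρ)/3: 252 suffices if ρ is at most (3 × 0.849 − 1)/2 = 0.77. At ρ = 0.5 the requirement is 198 per arm.

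Each route depends on a correlation that the protocol does not state.

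**The case against.** The best defence is that 73% belongs to a test the protocol does not plan. The analysis is a GEE over four time points with covariate adjustment, the power statement refers to follow-up time points in the plural, and PASS has procedures for repeated measures and for covariates. Several such analyses would exceed 80% at 0.23 with 252 per arm: adjustment for baseline at ρ = 0.5 gives about 85%, and the mean of three follow-ups suffices at any ρ up to about 0.77. The power of the trial's eventual analysis is therefore undetermined rather than shown to be 73%.

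That is right as far as it goes, and it is why stating the procedure and its correlation is an acceptable remedy. It does not rescue the sentence as written, which describes a between-arm effect size and gives none of these inputs. Nor do all readings help. The Data analysis section describes differential change over time, and a change-from-baseline contrast at one follow-up with ρ = 0.5 has the same 73%.

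It can also be said that dropout may stay below 20%, that GEE keeps partial data from those who leave, and that 0.23 and 0.25 are close. With no dropout at all, power at 0.23 is 82%. But the protocol attaches its 80% to 252 per arm, after the dropout allowance, and names 0.23 as the effect. Nor can the point be left to a statistical analysis plan: the protocol itself states the number, the effect, the power and the software.

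**Conclusion.** The concern holds. On the inputs the protocol states, 252 evaluable per arm gives 73% power at 0.23 and 77% at 0.24, not 80%. The number needed at 0.23 is 298 per arm (297 by the normal approximation), and the effect detectable with 80% power is 0.25.

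These figures assume an unadjusted two-sided 5% comparison of equal arms at one time point, with the full 20% lost. They would change if a baseline-adjusted or repeated-measures calculation was used, but the protocol does not say that one was. Because the power of the primary comparison rests on this paragraph, it must be corrected.

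**What to change.** Correct the sample size paragraph in one of two ways.

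1. Keep the enrolment target and restate the power: with 252 evaluable participants per arm, the trial has 80% power for a standardised difference of 0.25, 77% for 0.24 and 73% for 0.23, at a two-sided 5% level.
2. If 252 came from an adjusted or repeated-measures calculation, name the PASS procedure, the number of measurements and the correlation assumed, with its source. For a baseline-adjusted comparison at one follow-up, that correlation must be at least about 0.39 for 252 per arm to reach 80% at 0.23.

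In either case, state in the same sentence that the test is two-sided.

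The cost is one reworded paragraph and no added participants. Under the first option the stated power becomes less favourable. Keeping 80% power at 0.23 for an unadjusted comparison would instead mean enrolling 373 per arm rather than 315, or 2 × (373 − 315) = 116 more participants; correcting the text does not require this.
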